## Abstract

**Background:**

Chronic pain is highly prevalent in the working population. People tend to attempt self-initiated treatments to manage their pain. The self-efficacy of behavioural change is a suitable model for guiding the development of an electronic pain management programme (ePain). The aim in this study is to develop ePain and to evaluate its effectiveness at improving pain self-efficacy, reducing pain intensity and negative emotions, and increasing quality of life.

**Methods:**

This study will be a randomized controlled trial. ePain will take the form of a 6-week online pain management programme. Participants will be aged 15 years or above, have chronic pain, and be employed. They must complete the baseline questionnaire and will be randomized into intervention and control groups. They will receive notifications to encourage their participation in ePain and complete the evaluation questionnaires. They will complete the process evaluation at week 3, the post assessment at week 6, and the follow-up assessment at week 12. The study will focus on pain self-efficacy; pain situations; negative emotions including levels of depression, anxiety, and stress; and quality of life. The participants’ opinions of ePain will be collected as feedback. Data will be analysed on an intention-to-treat basis and generalized estimating equations will be used to investigate the time-averaged difference and differences at each follow-up time.

**Discussion:**

The study will provide information about the pain situations of online users in the working population. The participants will benefit from improvements in pain self-efficacy, pain situations, emotional status, and quality of life. The study will illustrate whether online learning is an effective intervention for improving the pain self-efficacy of the working population.

**Trial registration:**

ClinicalTrials.gov, NCT03718702. Registered on 23 October 2018.

## Background

The working population comprises the largest portion of people in Hong Kong society and is defined as adults aged from 15 to 64 years [1]. This group of people helps society to function. However, some of them continue to work despite experiencing pain.

Pain affects all age groups. It is defined as ‘an unpleasant and emotional experience associated with actual or potential tissue damage or described in terms of such damage’ [2]. Chronic pain is pain that persists for more than 3 months in an individual [3]. Pain is highly prevalent in the Hong Kong population. Studies have revealed that the prevalence of chronic pain ranges from 34.9% to 87.4%, and is high in people aged 18–64 years [4–6]. For the working population in particular, the prevalence of pain is 71.6% [4]. Common pain sites included the neck, bilateral shoulders, back, and extremities [4–6]. Mild to moderate pain intensity has been reported [4, 6]. The pain situation in the Hong Kong population is more serious than that in western countries. The prevalence of pain is reportedly 19% in the United States and 24.9% in Germany with mild intensity [7, 8], levels that are far below that in Hong Kong.

Pain can bring physical discomfort to sufferers and affect them psychologically. Depressive mood and anxiety have been found to be associated with the presence of pain [9, 10]. Patients with chronic pain develop and experience significant levels of depression and anxiety. Stress levels are also related to the presence of chronic pain [11–13]. Psychological stress and stress factors are associated with chronic non-specific neck–arm pain. Pain duration also influences a person’s stress level [12]. According to a longitudinal study, people who suffer from musculoskeletal pain and stress at the same time exhibit poorer working performance and ability [11]. In addition, chronic pain contributes negatively to the quality of life of patients. Surveys have revealed that chronic pain patients with multiple pain sites and pain-related difficulty in engaging in activities are likely to have a lower quality of life [14, 15]. Chronic pain patients have a lower quality of life than those who suffer from acute pain or no pain [16]. One survey focusing on the pain situation of the Hong Kong Chinese population showed that people with higher pain intensities exhibited higher levels of depression and anxiety and a lower quality of life [6].

People often use self-initiated treatments to manage their pain, including taking analgesics, exercising, and resting [17]. Instead of visiting accident, emergency, or outpatient departments, people either self-initiate treatments or use over-the-counter medications to treat their pain [5, 17]. Some even apply multiple treatments such as physiotherapy and traditional Chinese medicine [17, 18]. In addition, they perceive good effects from their self-initiated treatment [17]. Pain services are scarce in Hong Kong. Patients stay in their communities and see general practitioners or primary specialists before visiting pain specialists [18]. Therefore, to manage their pain and especially to meet their preference for pain self-management, it is essential to establish alternative means of targeting the working population. Promoting and enhancing self-efficacy in pain management may be the way to equip the working population with the knowledge and skills to manage their pain.

Self-efficacy is an important measure for determining whether patients can manage their health conditions [19]. Bandura’s self-efficacy theory of behavioural change is a classical model used to explain people’s perceptions and ability to actively participate in activities [20]. Self-efficacy is ‘people’s domain-specific perceptions of their ability to perform the actions necessary to achieve desired outcomes’ [21]. The self-efficacy theory of behavioural change explains how people’s beliefs and expectations contribute to their behaviour. People have their expectations when they engage in activities. When they engage in behaviours, they expect certain outcomes [20]. This leads them to actively participate in activities to achieve expected outcomes. Health promotion and disease prevention can be integrated with the self-efficacy theory of behavioural change [22]. Improving self-efficacy can modulate people’s health behaviour, and the maintenance of health behaviour can be promoted when people gain better control over their health problems. Health studies adopting the self-efficacy theory of behavioural change have demonstrated improvements in self-efficacy when managing chronic illnesses such as osteoarthritis, symptoms of heart failure, and obesity [23–25].

Therefore, in this study the self-efficacy theory of behavioural change will be adopted as the conceptual framework, taking advantage of eHealth, and an electronic pain management programme (ePain) will be designed as the intervention. eHealth is ‘the use of information and communication technologies for health’ [26]. The benefits of using eHealth include an increase in efficiency; enhancements in quality; patient empowerment, encouragement, and education; the exchange of information and communication; and overcoming of the barriers to obtaining health services [27, 28]. With the advancement and advantages of eHealth, people can obtain health education information from the Internet without the limitations of geography and time [29]. Web-based programmes have shown success in enhancing the disease knowledge and self-management abilities of patients with type 2 diabetes, fibromyalgia, and chronic pain [30–32]. There is currently no electronic pain management system that has been tailor-made for the working population and that is in the Chinese language. An electronic pain management programme can meet the demands and service needs of the working population with chronic pain, especially when the population is well equipped with the knowledge to access the Internet and use electronic devices.

### Objectives

This study will aim to develop and evaluate the effectiveness of ePain in improving self-efficacy; reducing pain intensity; decreasing levels of depression, anxiety, and stress; and improving the quality of life of adults seeking to manage chronic pain.

## Methods: participants, interventions, and outcomes

### Trial design and study setting

A two-group, randomized controlled trial will be conducted. ePain will be implemented online to help chronic pain participants self-manage their pain. The participants will be randomized into intervention or control groups. The study protocol will follow the Standard Protocol Items: Recommendations for Interventional Trials (SPIRIT) Statement.

### Preparatory phase

An extensive literature search on pain management methods will be conducted. An online survey will be carried out to collect the preferences and views of the working population on the use of electronic pain management materials. The contents of ePain will be generated by a combination of the literature search and the results of the online survey. The contents will be validated by an expert panel comprising a doctor, a pain nurse, a physiotherapist, and an occupational therapist. Five chronic pain participants who are members of the working population will be recruited to conduct a usability test. Their understanding of the contents of ePain will be examined and their feedback on it will be collected. Their comments and suggestions will be used to improve ePain. The participants will attend a briefing session to understand the objectives of the study, and the applications and functions of ePain. The participants will access ePain with the testing account and password. They will then complete the Computer System Usability Questionnaire to provide information on their user experience and overall evaluation of ePain [33].

### Interventions

#### Conceptual framework

This study will adopt the self-efficacy theory of behavioural change as its conceptual framework. Participants joining ePain will expect to improve their pain knowledge and pain management techniques. Their expectations of the efficacy of pain management will then increase. Their self-efficacy will continually improve and this will strengthen their resolve to continue participating in ePain. Through their repeated use of ePain, their expectations of the outcome will lead to a decrease in the intensity of their pain; reduce their levels of depression, anxiety, and stress; and improve their quality of life.

#### Contents of ePain

The participants will register accounts using their e-mail addresses. An e-mail address and password will be required for every login. After registration, the participants will finish the baseline assessment. They will be asked to identify the most painful sites in their body. Based on the participants’ choices, ePain will provide a tailor-made pain site response message when they first enter ePain. The locations of the relevant content will be shown and the participants will be encouraged to visit the content that fits their needs.

The contents of ePain will focus on self-directed learning about pain knowledge and self-management techniques. Three sessions will cover the self-directed learning of pain knowledge and four sessions will cover self-management techniques. These will include ‘Introduction to pain’, ‘Pain related diseases and syndromes’, ‘Occupational diseases related to pain’, ‘How to manage your pain’, ‘Pharmacological approaches to pain management’, ‘The non-pharmacological management of pain’, and ‘Exercise for relieving pain’.

In the sessions on self-directed learning about pain knowledge, the participants will learn the definition of pain, pain theories, the factors contributing to pain, and how pain contributes to an individual’s physicality and psychology. Diseases, syndromes, and occupational diseases in which pain is presented will also be included.

In the session on self-management techniques, evidence-based pharmacological and non-pharmacological interventions will be introduced. The participants will learn about the World Health Organization’s Pain Relief Ladder [34]. Commonly used analgesics such as paracetamol and tramadol will be included. The use of medications, including dosages, side effects, and precautions, will be discussed. Non-pharmacological interventions for pain management such as aromatherapy, massage, and deep breathing exercises will be introduced [35–38]. The participants will be able to view photographs and video demonstrations of pain relief and prevention exercises in ePain. Pain management will also be introduced from the perspective of Chinese medicine. In addition, the participants will learn how to plan their own pain management interventions.

The participants will click the option ‘I understand the contents of the chapter’ to proceed with the quiz. A quiz will be administered at the end of each chapter to ensure that the participants read ePain and understand the chapter. The questions will be generated from the contents of the chapter. The expert panel will review the questions and the chronic pain participants recruited in the preparatory phase will try out the quizzes and provide feedback. Six true/false questions will cover the contents in each chapter. The participants will complete the quiz and the results will be displayed immediately and recorded in ePain. Those participants who had low marks will be contacted through e-mail to remind them to read the contents again.

The ePain platform will provide a portal for the participants to record their experiences and learning on the management of their pain. The use of pharmacological and non-pharmacological methods of pain management will be recorded on a checklist, which will include the type of intervention, the frequency of usage per day and per week, and the perceived effectiveness of the intervention. Individualized records will be saved in ePain, and the participants will be able to retrieve the records.

ePain will be designed in an interactive, colourful, and user-friendly way. The contents will be easy to read. ePain will be presented in traditional Chinese characters.

ePain will offer a message column for the participants to contact the researcher when they are in doubt and provide comments on the use of ePain. E-mails will be sent at weeks 3, 6, and 12 to prompt the participants to complete the assessments. The participants will receive e-mails in subsequent weeks as a weekly reminder to finish the assessments. A function that sends the ePain link to others will be provided to invite new participants.

### Eligibility criteria

The criteria for inclusion in this study are adults aged 15–65 years, with 65 years being the normal retirement age for civilian officers [39]. The participants will have held a formal job or worked for pay or for profit during the 7 days prior to the study [1]. They will be able to read and understand traditional Chinese characters. They will have had non-cancer chronic pain for at least 3 months and scored 1 or higher on a 10-point numeric pain-intensity rating scale in the Chinese version of the Brief Pain Inventory (BPI-C). They will need to own a computer and a mobile phone, and be able to use the devices to access ePain.

### Recruitment

Participants will be recruited through social network webpages, e-mails sent to companies and workers’ organizations, and posters at the university. Information about the study, including the objectives, procedure, duration, and website of ePain, will be shown in the recruitment materials.

### Randomization

The study will use permuted block randomization. A block size of four and an allocation of 1:1 will be adopted. The sequences that have been generated are AABB, ABAB, ABBA, BAAB, BABA, and BBAA, with A as the intervention group and B as the control group. The block sequence will be programmed to ePain and run randomly. The research team cannot modify the sequence and randomization of the sequence in ePain. The team will be blinded to the sequence used to allocate the participants. When the participants register for ePain, they will be assigned at random according to the sequence, and blinded to the sequence.

### Intervention group

The participants in the intervention group will enter ePain after completing the baseline assessment and randomization at week 1. They will be able to access all of the contents of ePain throughout the study period. They will complete the process evaluation at week 3, the post assessment at week 6, and the follow-up assessment at week 12.

### Control group

The control group participants will be able to download a pain education pamphlet after completing the baseline assessment. The pain pamphlet will contain information from the session ‘Introduction to pain’, which will discuss the definition of pain, pain theories, and factors contributing to pain. They will also need to complete the post assessment at week 6 and the follow-up assessment at week 12. ePain will be open to the participants after they complete the follow-up assessment.

### Outcomes

#### Primary outcome

The primary outcome is pain self-efficacy, which will be measured using the Pain Self-Efficacy Questionnaire at weeks 1, 3, 6, and 12. The questionnaire will contain 10 items. A 7-point scale will be used for measurement, ranging from 0 (not at all confident) to 6 (completely confident), with higher marks representing stronger self-efficacy beliefs. The Cronbach’s α coefficient of the measure of the internal consistency of the items is 0.92 [40]. The Chinese version of the Pain Self-Efficacy Questionnaire (PSEQ-HK) has a Cronbach’s α coefficient of 0.93. Its test–retest reliability coefficient is 0.75, and the SF-36BP and the PSEQ-HK are significantly correlated, with *r* = 0.402 [41].

#### Secondary outcomes

Secondary outcomes will include the measurements for pain situations, negative emotions, quality of life, and the feedback from the participants. The BPI-C, which reports the pain intensity and interfaces of pain in a patient’s life, will be used to measure the pain situations of the participants [42]. It has been validated for use in chronic pain patients [43]. The BPI-C has four pain severity scales and seven pain interference measurements, rated on a scale from 0 (no pain) to 10 (pain as bad as you can imagine). The Cronbach’s α coefficient for pain severity is 0.894 and that for pain interference is 0.915 [42].

The Depression Anxiety Stress Scale (DASS-21) will be used to assess the participants’ levels of negative emotion, including depression, anxiety, and stress [44]. The DASS-21 includes three subscales for depression, anxiety, and stress, respectively, with seven items in each subscale. The scores can reflect the following five grades of depression, anxiety, and stress: normal, mild, moderate, severe, and very severe. The DASS-21 was found to have satisfactory internal consistency with reliability, with *p* = 0.94; while for the depression scale *p* = 0.87, for the anxiety scale *p* = 0.69, and for the stress scale *p* = 0.89 [45]. A Chinese version of the DASS-21 is available. The φ coefficients between the depression, anxiety, and stress scales in the confirmatory factor analysis were 0.92 for depression–anxiety, 0.94 for anxiety–stress, and 0.91 for depression–stress [46].

The participants’ quality of life will be reported using the Hong Kong Chinese version of the World Health Organization Quality of Life Instruments (WHOQOL-BREF (HK)) [47]. Two questions and four domains (physical health, psychological health, social relationships, and environment) containing a total of 28 items will address overall quality of life and health condition [47, 48]. A 5-point scale is adopted in the WHOQOL-BREF (HK). The Cronbach’s α coefficients for the four domains were found to be satisfactory, with 0.77 for physical health, 0.8 for the psychological health, 0.59 for social relationships, and 0.76 for the environment. The inter-rater reliability ranged from 0.8 to 0.91 for the four domains [47].

Open-ended questions will be used to collect comments from the participants, including comments on user experience, the design of the webpage, the usefulness of ePain, and items for improvement.

### Sample size

The sample size was estimated based on Ruehlman et al. [30], who aimed to examine an Internet-based programme for the self-management of chronic pain in the United States. Their measure of pain intensity was used to calculate the effect size, as their study did not examine self-efficacy. The effect size was calculated to be 0.47. To achieve an effect size of 0.47, a power value of 0.8, and an α value of 5%, 114 participants will be recruited. The drop-out rate has been calculated with reference to Ruehlman et al.’s study examining the efficacy of an online Chronic Pain Management Programme and William et al.’s study evaluating the effects of an Internet-based behavioural self-management programme on fibromyalgia patients [30, 31]. The drop-out rate was 7.5% in Ruehlman et al.’s study and 10% in William et al.’s study [30, 31]. A 30% drop-out rate needs to be considered to obtain an adequate number of participants. Therefore, 148 participants will be recruited, with 74 participants in each group.

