### Statistical methods

The IBM Statistical Package for the Social Sciences (SPSS) for Windows version 25.0 will be used to statistically analyse the quantitative data. Normality checking will be conducted using the Kolmogorov–Smirnov test. For the descriptive data on the demographics and outcome variables, the means, standard deviations, and percentages will be calculated. For continuous variables, the mean and standard deviations will be presented. The median and a centile range will be reported if the continuous variables do not show a symmetrical distribution.

The data will be analysed on an intention-to-treat basis. Generalized estimating equations will be adopted to investigate the time-averaged difference and differences at each follow-up time. An analysis will be conducted of the within-group effect at week 3, week 6, and week 12, and the interaction between the time effect and the group by group effect (group × time) on the outcome variables, including pain self-efficacy, pain situations, negative emotions, and quality of life. An independent-samples *t* test will be conducted for between-group comparisons at week 3, week 6, and week 12. The significance level will be set at 0.05. Missing data will be analysed using Missing Values in SPSS. The last observation carried forward method will be used to replace the missing data [49, 50].

The Consolidated Standards of Reporting Trials (CONSORT) will be adopted to write up the final report.

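### The 114 participants match a one-sided 5% test that the protocol never declares; under a two-sided 0.05 t test at one visit, 114 give about 70% power, not 80%

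*Protocol article*

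**What the plan says.** The Sample size section takes its effect size from pain intensity in a cited trial of an online programme: "The effect size was calculated to be 0.47". It then fixes the number: "To achieve an effect size of 0.47, a power value of 0.8, and an α value of 5%, 114 participants will be recruited". It adds an allowance for loss, "A 30% drop-out rate needs to be considered to obtain an adequate number of participants", and concludes: "Therefore, 148 participants will be recruited, with 74 participants in each group". The Randomization section gives equal allocation: "A block size of four and an allocation of 1:1 will be adopted".

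The Statistical methods section names two kinds of between-group analysis. The first is a GEE model: "Generalized estimating equations will be adopted to investigate the time-averaged difference and differences at each follow-up time". The second is an independent-samples t test at single visits: "test will be conducted for between-group comparisons at week 3, week 6, and week 12". One level covers everything: "The significance level will be set at 0.05". Neither section says whether the 5% or the 0.05 is one-sided or two-sided, and the rest of the protocol does not say so either.

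**The concern.** Effect size, power, alpha and sample size are stated together, so any three fix the fourth. With the usual two-sided 5%, the stated effect size and power call for clearly more than 114. The figure fits a one-sided 5% instead, and a reader has no way of knowing that.

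Two things are at stake. First, a null result would be read as coming from a trial with 80% power when, for a two-sided single-visit comparison at the stated number, it is nearer 70%. Second, while sidedness is undeclared, the choice stays open after the data are seen. A one-sided 0.05 test puts 5% in the favourable direction where a two-sided test puts 2.5%.

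**Working it through.** **Inputs.** Standardised difference d = 0.47, power 0.80, alpha 5% and N = 114 (Sample size); 1:1 allocation (Randomization), so 114 / 2 = 57 per group; analysis level 0.05 (Statistical methods). Sidedness is not given, so both cases are run.

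**Step 1: reproduce 114.** The normal approximation is n per group = 2(z_α + z_β)² / d², with z_β = 0.842 for 80% power and d² = 0.2209.

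- One-sided 5%, z_α = 1.645: 2 × (1.645 + 0.842)² / 0.2209 = 56.0, so 56 per group, 112 in total.
- Two-sided 5%, z_α = 1.960: 2 × (1.960 + 0.842)² / 0.2209 = 71.1, so 72 per group, 144 in total.

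The t test itself (noncentral t) gives:

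- One-sided: 56.66, so 57 per group, **114 in total**. This is the plan's figure exactly, with power 0.802.
- Two-sided: 72.04, so 73 per group, **146 in total**.

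Rounding of d does not close the gap: at d = 0.475 the two-sided t test still needs 70.5, so 71 per group.

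**Step 2: two-sided power at the plan's numbers.** The noncentrality is d × √(n/2); for 57 per group it is 0.47 × √28.5 = 2.51. All figures are for an unadjusted t test at one visit, two-sided 0.05, d = 0.47.

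| Analysed per group | Total | Power | Effect detectable with 80% power |
|---|---|---|---|
| 57 | 114 | 0.701 | 0.529 SD |
| 74 (no loss from 148) | 148 | 0.811 | 0.464 SD |
| 52 (30% lost, completers only) | about 104 | 0.661 | 0.555 SD |

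The last row comes from 148 × 0.7 = 103.6, about 52 per group. With a one-sided 5% test, power in that row would be 0.769.

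**Step 3: could the GEE contrast explain 114?** For the mean of two follow-ups (weeks 6 and 12, which both groups complete) with within-person correlation r, the variance is multiplied by (1 + r)/2. The protocol gives no r for this purpose, so the values below are assumptions. Two-sided power at 57 per group is then:

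- r = 0.3: 0.87
- r = 0.5: 0.82
- r = 0.6: 0.79
- r = 0.75: 0.76

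A correlation near 0.6 would bring the two-sided need close to 114. However, the Sample size section mentions neither a correlation nor a number of measurements, so this is not a derivation that the document supports. It does show that 0.70 is not the power of every planned analysis.

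**The case against.** The strongest reply is that the protocol contradicts itself nowhere in words. It never says two-sided, and 57 per group with a one-sided 5% test does have 80% power. A reader might infer that the plan commits to two-sided tests and that the stated power is therefore simply wrong. The documents do not support that, because two-sided testing is an inference. It is a strong one: an unqualified 0.05 is conventionally two-sided, the group-by-time test named in the Statistical methods section is normally non-directional, and no one-sided hypothesis is declared or justified. If one-sided tests were intended, an undisclosed choice drives the sample size, and the text still needs correcting.

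A reader might also take 70% as the power of the trial. It belongs to an unadjusted t test at one visit. As step 3 shows, the GEE time-averaged contrast could have power above or below 80%.

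The 66% is conditional too. The Statistical methods section plans intention to treat with last observation carried forward, so nominally all 148 are analysed, which gives 81%; carrying values forward could dilute the effect. The drop-out rates cited in the Sample size section are 7.5% and 10%, not 30%. At 10% loss about 66 per group remain, with two-sided power about 0.76 if only completers count.

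Finally, the Discussion concedes that the sample size may be too small or too large. That caveat concerns the effect size, which was borrowed from pain intensity. The mismatch here exists with d = 0.47 taken as true.

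**Conclusion.** The point holds in a conditional form. From the inputs the protocol states, 114 is a one-sided 5% sample size, and the protocol does not say so. If the 0.05 level is two-sided, as convention suggests, a t test at one visit has about 70% power with 114 analysed, and 80% power needs 146, which is 32 more. The planned 148 would reach about 81% if every participant contributes, and about 66% if 30% are lost and only completers contribute.

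These figures assume d = 0.47 in units of the SD of a single score, equal groups and no baseline adjustment. They do not establish the power of the GEE contrast.

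**What to change.** State in the Statistical methods section that all tests are two-sided at 0.05. Rewrite the Sample size section to say that:

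- 146 analysed (73 per group) are needed for 80% power at d = 0.47 with a two-sided t test at one visit;
- the planned 148 give about 81% if all are analysed, and about 66%, with a detectable effect of about 0.56 SD, if 30% are lost and only completers (about 52 per group) contribute;
- these figures are for a single-visit unadjusted comparison, and the power of the GEE time-averaged contrast depends on a within-person correlation that the protocol does not give.

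No further enrolment is asked for; the Trial status section reports that recruitment closed on 1 January 2020. A baseline-adjusted model might change the power, but the Statistical methods section specifies none, so it would be a separate change of analysis. The way the 30% was added (114 × 1.3 = 148.2, where 114 / 0.7 would give 163) is also a separate matter. The cost is wording and a less favourable stated power.

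### The sample size treats drop-outs as lost cases, but the planned analysis keeps them in with carried-forward scores; the dilution this can cause is not allowed for in the stated 80% power

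*Protocol article*

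**What the plan says.** The Sample size section of the protocol article takes its effect from pain intensity in a cited online trial: "The effect size was calculated to be 0.47". It then gives the base number: "To achieve an effect size of 0.47, a power value of 0.8, and an α value of 5%, 114 participants will be recruited". Drop-out in the two cited studies was 7.5% and 10%, but the section allows for more: "A 30% drop-out rate needs to be considered to obtain an adequate number of participants. Therefore, 148 participants will be recruited, with 74 participants in" either arm.

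Statistical methods sets the analysis: "The data will be analysed on an intention-to-treat basis". For missing values: "The last observation carried forward method will be used to replace the missing data". The comparisons are generalized estimating equations (GEE), giving a time-averaged difference, differences at each follow-up and a group by time interaction, together with independent-samples t tests at each visit. The level is 0.05, with no sidedness stated.

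Data collection methods fixes which scores can be carried. Baseline, week 6 and week 12 are collected in both groups. Week 3 is described as a process evaluation in the intervention group.

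**The concern.** Adding recruits for drop-out assumes that those who leave drop out of the analysis and that those who remain show the full 0.47. The written analysis does something else. Nobody leaves it. An ePain participant who stops early enters later visits with an earlier score, which may hold none, part or all of the effect. Where it holds less than all, the group difference shrinks. Power depends on the number analysed times the square of the difference, so adding recruits in proportion to drop-out does not make up for a smaller difference.

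The trial's only power statement therefore describes an analysis set that the plan does not use. If drop-out comes near the allowed 30%, a null result on pain self-efficacy would be read against 80% power, when power under the written analysis could be well below that.

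**Working it through.** **Inputs.** From Sample size: effect 0.47, power 0.8, α 5%, base 114, drop-out allowance 30%, final 148 (74 per group), cited drop-out 7.5% and 10%. From Statistical methods: intention-to-treat, last observation carried forward, independent-samples t test. Not in the documents: the share k of the effect that a drop-out's carried score retains. It is varied from 0 to 1.

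**Reproducing the plan's figures.** For a two-sample t test at d = 0.47, 80% power and α = 0.05:
- One-sided: 56.7, so 57 per group, which is 114 and matches the plan.
- Two-sided: 72.04, so 73 per group, which is 146 and does not match.
- At 57 per group, power is 80.2% one-sided and 70.1% two-sided.
- 114 × 1.3 = 148.2, which gives the plan's 148. Dividing instead, 114 / 0.7 = 162.9, so 163.

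**If drop-outs really were lost.** 148 × 0.7 = 103.6 analysed, about 52 per group, with the full effect. Power is 65.9% two-sided and 76.8% one-sided. This shortfall comes from sidedness and the × 1.3 step, not from dilution.

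**Under the written analysis.** All 74 per group are analysed. With drop-out proportion p in both groups and no change in controls, the diluted effect is

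d* = 0.47 × (1 − p + p·k)

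| p | k | d* | Power, two-sided | Power, one-sided |
|---|---|---|---|---|
| 30% | 0 | 0.329 | 51.1% | 63.6% |
| 30% | 0.25 | 0.364 | 59.5% | 71.2% |
| 30% | 0.5 | 0.400 | 67.5% | 78.1% |
| 30% | 0.75 | 0.435 | 74.8% | 83.8% |
| 30% | 1 | 0.470 | 81.1% | 88.5% |
| 10% | 0 | 0.423 | 72.4% | 82.0% |
| 7.5% | 0 | 0.435 | 74.8% | 83.8% |

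For 80% power at 30% drop-out, carried scores must keep about 58% of the effect (one-sided) or about 95% (two-sided).

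**How much is due to dilution.** Compare the worst case (p = 30%, k = 0) with simple loss at 30%: two-sided 65.9 − 51.1 = 14.8 points; one-sided 76.8 − 63.6 = 13.2 points.

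**Does dividing by 0.7 cure it?** With 82 per group (164 in all) and k = 0, power is 55.3% two-sided and 67.5% one-sided. It does not.

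**Group by time contrast.** This compares change from baseline, so its power depends on the baseline to follow-up correlation. Simulating the worst case (30% drop-out in both groups, baseline carried forward, 0.47 in raw SD units, 74 per group, 20,000 trials) gives two-sided / one-sided power of about 51% / 64% at correlation 0.3, 65% / 76% at 0.5, 75% / 84% at 0.6 and 91% / 95% at 0.75. The documents give no baseline to follow-up correlation. The 0.75 in Primary outcome is a test–retest coefficient.

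**The case against.** A reader might infer that this plan has only 51% to 64% power at its own 30% drop-out. The documents do not support that as a flat statement, for four reasons.

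- **It is the no-effect case.** Week 3 scores in the ePain group and week 6 scores in both groups can be carried forward, so a participant lost after week 6 brings a real post-programme score to week 12. There is a limit to this: at week 6 itself an ePain drop-out can carry only a baseline or week 3 score, so full retention at that visit would need the whole effect to be present by week 3.
- **The t test is not the only planned comparison.** The group by time contrast can pass 80% even in the worst case if scores correlate strongly over time. This stands, and any restated figure must say which comparison it is for. The Sample size section itself claims no gain from repeated measures.
- **The completer reading of 0.47 is inferred.** It follows from how drop-out is added, and is not stated. If 0.47 already reflects the cited trial's 7.5% drop-out, the extra dilution at k = 0 is 0.70 / 0.925 = 0.76, so d* is about 0.36 and power is close to the k = 0.25 row.
- **Setting 51% against 80% mixes faults.** Two-sided power at 114 is already 70.1% with no drop-out at all.

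It can also be said that at the cited 7.5% to 10% drop-out, one-sided power stays above 80%, and that the Discussion already warns that the sample size may be too small or too large. The first is true, but the protocol chose to plan for 30%. The second concerns the unknown effect on self-efficacy, not the missing-data rule.

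**Conclusion.** The mismatch is real: drop-out is allowed for as lost cases, while the analysis keeps every randomised participant with a carried score, and nothing in the sample size covers the dilution that can follow. For the single-visit t test at 30% drop-out, power runs from about 51% / 64% (two-sided / one-sided) with no effect carried to about 81% / 89% with all of it carried. Only 13 to 15 points of the worst-case shortfall belong to this point.

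The figures assume equal drop-out in both groups, no change in controls, an unchanged SD, and 0.47 as the effect in those who stay. The documents do not settle where in the range the trial lies. They do not support 80% power at 30% drop-out without conditions, and they do not support the lowest figure as the plan's power.

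**What to change.** In Sample size, state power for all 148 randomised under the planned analysis, as a range over drop-out rate and share of effect carried, and name the sidedness. Suggested wording: 'With 74 per group, a single-visit t test and 30% drop-out, power to detect 0.47 SD in those who stay is about 51% (two-sided 5%) or 64% (one-sided 5%) if carried-forward scores show no effect, 68% or 78% if they keep half of it, and 81% or 89% if they keep all of it. At 7.5% to 10% drop-out with no effect kept, it is about 75% to 72% or 84% to 82%. The group by time contrast may have higher power, depending on the correlation between baseline and follow-up scores.'

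Do not present 148 as securing 80% power at 30% drop-out without these conditions, and read a null result on pain self-efficacy against the restated range. The sidedness and the × 1.3 step need their own corrections.

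The cost is one rewritten paragraph and a less favourable power statement. Recruitment is complete, and no new participants or data are needed.
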